## Abstract

**Background:**

While arthritis is the most common cause of disability, non-Hispanic blacks and Hispanics experience worse arthritis impact despite having the same or lower prevalence of arthritis compared to non-Hispanic whites. People with arthritis who exercise regularly have less pain, more energy, and improved sleep, yet arthritis is one of the most common reasons for limiting physical activity. Mind-body interventions, such as yoga, that teach stress management along with physical activity may be well suited for investigation in both osteoarthritis and rheumatoid arthritis. Yoga users are predominantly white, female, and college educated. There are few studies that examine yoga in minority populations; none address arthritis. This paper presents a study protocol examining the feasibility and acceptability of providing yoga to an urban, minority population with arthritis.

**Methods/design:**

In this ongoing pilot study, a convenience sample of 20 minority adults diagnosed with either osteoarthritis or rheumatoid arthritis undergo an 8-week program of yoga classes. It is believed that by attending yoga classes designed for patients with arthritis, with racially concordant instructors; acceptability of yoga as an adjunct to standard arthritis treatment and self-care will be enhanced. Self-care is defined as adopting behaviors that improve physical and mental well-being. This concept is quantified through collecting patient-reported outcome measures related to spiritual growth, health responsibility, interpersonal relations, and stress management. Additional measures collected during this study include: physical function, anxiety/depression, fatigue, sleep disturbance, social roles, and pain; as well as baseline demographic and clinical data. Field notes, quantitative and qualitative data regarding feasibility and acceptability are also collected. Acceptability is determined by response/retention rates, positive qualitative data, and continuing yoga practice after three months.

**Discussion:**

There are a number of challenges in recruiting and retaining participants from a community clinic serving minority populations. Adopting behaviors that improve well-being and quality of life include those that integrate mental health (mind) and physical health (body). Few studies have examined offering integrative modalities to this population. This pilot was undertaken to quantify measures of feasibility and acceptability that will be useful when evaluating future plans for expanding the study of yoga in urban, minority populations with arthritis.

**Trial registration:**

ClinicalTrials.gov: NCT01617421

## Background

In order for an intervention to be used, it must be acceptable to participants, and it must be feasible to administer. Acceptability can be defined as, “that quality which makes an object, person, event, or idea attractive or satisfactory” [1]. Factors highly likely to be influential in shaping values and perceptions include ethnicity, nationality, culture, education, personality, and experience [2]. The purpose of this pilot study is to investigate the feasibility and acceptability of offering a yoga intervention to the urban, minority population served by the National Institute of Arthritis and Musculoskeletal and Skin Disease (NIAMS) Community Health Clinic (CHC) serving the Washington, DC area.

Previous studies using data from the 2002 National Health Interview Survey (NHIS)-Alternative Medicine Supplement found that yoga users were predominately white, female, and college educated with a mean age of 39.5 years [3]. Among those reporting using yoga, 12% were black or Hispanic, 88% stated place of birth as the United States, and 27% used yoga for joint pain [4]. There are a few studies in the literature that examine yoga in minority or diverse populations but none specifically address patients with rheumatic disease [5-7].

This study is a follow-up intervention to a descriptive, exploratory study, completed in 2004 by Wallen et al. (Clinical Trial# http://NCT00069342) which examined the diverse health beliefs and behaviors among a convenience sample of primarily African-American and Hispanic patients enrolled in the NIAMS Natural History of Rheumatic Disease in Minority Communities protocol [8-10]. Overall complementary and alternative medicine (CAM) usage was high, with pain relief listed as the primary reason. A little more than one-third (39%) of respondents stated that they were currently doing movement activity, and only 4.6% stated they were doing yoga [11].

Arthritis is highly prevalent in US adults, with approximately 50 million persons reporting doctor-diagnosed arthritis [12]. Furthermore, arthritis is the nation’s most common cause of disability and is associated with considerable activity limitation, work disability and significant health care costs [13]. The most common form of arthritis is osteoarthritis (OA), a slowly progressive joint disease that occurs when the joint cartilage breaks down. OA symptoms include joint pain, stiffness, knobby swelling, cracking noises with joint movements and decreased function. It typically affects the joints of the hands and spine and weight-bearing joints such as the hips and knees [14,15]. Another form of arthritis is rheumatoid arthritis (RA), an autoimmune, chronic disease that causes pain, stiffness, swelling and limitations in the motion and function of multiple joints. While RA can affect any joint, the small joints in the hands and feet tend be involved more frequently than others [15,16].

Arthritis disproportionally affects certain racial/ethnic minorities. The prevalence of arthritis is lower among blacks and Hispanics than among whites, but the impact is worse. Published analysis of racial/ethnic differences from the NHIS shows the prevalence of activity limitation, work limitation and severe joint pain are significantly higher among blacks, Hispanics, and multi-racial or “other” respondents than among whites [17,18]. People with arthritis should be moving according to the American College of Rheumatology, the Arthritis Foundation and the Centers for Disease Control and Prevention (CDC) [19-21]. People with arthritis who exercise regularly have less pain, more energy, improved sleep and better day-to-day function. Yet, arthritis is one of the most common reasons people give for limiting physical activity and recreational pursuits [20]. People with arthritis may have a difficult time being physically active because of symptoms and lack of confidence in knowing how much and what to do [21]. Long-term studies have shown that people with inflammatory arthritis such as rheumatoid arthritis can benefit from moderate intensity, weight-bearing activity [22]. According the CDC, physical activity can reduce pain and improve function, mobility, mood, and quality of life for most adults with many types of arthritis and recommends including activities that improve balance for people with arthritis who may be at risk for falling [21]. According to the American College of Rheumatology, both range-of-motion (ROM) and stretching exercises help to maintain or improve the flexibility in affected joints and surrounding muscles. This contributes to better posture, reduced risk of injuries and improved function. They recommend activities such as yoga because it incorporates both ROM and stretching movements [22]

According to a report using the data from the 2002 NHIS, adults with arthritis are significantly less likely to engage in recommended levels of physical activity. In both men and women with arthritis, inactivity has been associated with older age, lower education, and having functional limitations. Access to a fitness facility was inversely associated with inactivity. Among women, inactivity was also associated with being Hispanic, non-Hispanic black, having frequent anxiety/depression or social limitations, needing special equipment to increase functional capacity, and not receiving physical activity counseling [23].

Yoga is an ancient system of relaxation, exercise, and healing with origins in Indian philosophy an estimated 5,000 years ago [24,25]. It is regarded as a holistic approach to health reported to increase flexibility, strength, and stamina while also fostering self-awareness and feelings of well-being [26-33]. Yoga can be done anywhere, requires no special equipment, is gentle on the joints and can be modified for each person. It uses only gravity and the body itself as resistance, so it is a low-impact activity. However it is not just an exercise; it is a mind-body intervention. The combination of stress management and gentle physical activity is well suited for investigation in both osteoarthritis (OA) and inflammatory immune-mediated diseases such as rheumatoid arthritis (RA) [34].

Yoga is generally low-impact and safe for healthy people when practiced appropriately under the guidance of a well-trained instructor.  Overall, those who practice yoga have a low rate of side effects, and the risk of serious injury from yoga is quite low [24]. As with any physical activity based on the person undertaking the exercise, there may be contraindications or side effects which make a technique (such as postures or breath work) inadvisable [24,25]. For example poses that put the head lower than the heart may lead to increases in cerebral and intraocular pressure; therefore, patients with high myopia or with hypertension, glaucoma, detachment of the retina, central retinal vein occlusion, discharging ears, or cervical spondylitis should avoid some inverted poses [24,25]. Adverse events and case reports found in the literature were reviewed when preparing the protocol [3,35-37]. However, related poses and techniques reported are not taught or encouraged as part of this protocol. All patients for this study are medically cleared to participate in light to moderate exercise before being recruited to participate.

According to the yogic literature, yoga can help correct the interconnected factors of dysfunctional movement patterns, lack of body awareness, and poor posture [15,26,38]. Yoga takes the whole body through a wide range of motion [15]. Static stretching is the most common technique used in Hatha yoga; which includes both contracting muscles to stretch a target muscle, and when relaxing into a stretch using only body weight to stretch muscles [39]. People with arthritis tend to avoid using sore joints because of the pain involved; inactivity weakens muscles and further decreases range of motion in the joints. Gentle movement taught by a skilled yoga therapist may help by keeping the body moving. Yoga may be suited to help prevent or minimize the erosion of cartilage that causes the joint pain of OA, to create greater ease of movement and decrease pain within joints that have already sustained damage [15]. Most descriptions of the effect of yoga on musculoskeletal disorders point to the benefits of joint realignment and active stretch producing traction of muscles during the asanas (or yoga poses) [40].

A growing number of research studies have shown that the practice of yoga can improve posture, strength, endurance and flexibility [31,41,42]; improve balance, gait, and fear of falling [43-45], and hand grip strength [46]. Other studies have shown that practicing yoga asanas (postures), meditation or a combination of the two, reduces pain for people with arthritis [47,48]. Yoga postures and breath work (pranayama) have been shown to also help with physiological variables such as blood pressure, respiration, and heart rate [47-57]. For patients with arthritis, emphasis on stretching, strength, posture, balance, and the ability to adjust pace and intensity are important components of a safe activity, all of which yoga encompasses. Yoga interventions have been shown to produce improvements in quality-of-life measures related to sense of well-being, energy, and fatigue [58]; and to beneficially impact mood, depression and anxiety disorders [28-33]. Yoga has also been demonstrated to reduce the physical effects of stress [59,60], by reducing the levels of cortisol [61-64]; and affecting the neuroendocrine system [65]. Stress may play a role in worsening symptoms of OA, and contribute to flare-ups of inflammation in RA [15]. There is promising evidence that yoga therapy may help both osteoarthritis and rheumatoid arthritis [25,44,66-75]. The most important limitations of the existing research regarding the impact of yoga are: lack of minority representation, inadequate sample size, overly broad age range, lack of specification regarding the tradition of yoga utilized, and lack of a theoretical model to inform treatment implementation and assessment of outcomes [76].

There are studies that report an interest of diverse minorities in complementary and alternative medicine (CAM) [7] and that CAM is most often used to treat a variety of musculoskeletal problems and conditions [77]. The question to ask is, why not yoga? It is possible that culture plays an important role in the initiation of yoga use and other forms of physical activity. For example, one study found that Latina women’s physical activity depended on their degree of acculturation, expounding that for many the concept of “leisure time,” does not exist. And that middle-class Latinos work five extra hours per week compared with Anglo-Americans [78]. Disparities in the use of yoga in minority groups (specifically low-income populations) could be related to the costs of attending classes. One of the most practiced CAM modalities is prayer, a practice that is financially accessible to all income levels [7,47]. Given that yoga practice can be a fee-based service, it might be challenging for low-income populations to use this health modality. Geographical access to yoga classes may also be problematic for disadvantaged populations. However, a study by Wilson (2008) suggests that given access to yoga practices, diverse populations benefit from these practices, and anticipate using them in everyday life. Almost all participants in this study (98%) would recommend yoga practices to others [7].

The primary objective of this study is to determine the feasibility and acceptability of providing yoga to an urban, minority population with arthritis, using a proven yoga based intervention. The secondary objective is to determine the appropriateness of specific physical and psychosocial measures for this population, and intervention with a focus on physical function and patient reported measures. The tertiary objective is to determine the feasibility of using computerized self-interview (with assistance) to capture baseline and final status.

Assessments will be made from a convenience sample of 20 participants undergoing an 8-week program of yoga classes consisting of 60-minute sessions, twice a week. The yoga classes are designed especially for people with arthritis.

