The primary aim of this pilot study is to attempt to quantify measures of feasibility and acceptability that will be useful when evaluating future plans for expanding the study of yoga in this population. There are a number of challenges in recruiting and retaining study participants in a community setting. We hypothesize that by providing bilingual materials, racially concordant images for recruitment materials, culturally similar investigators and yoga instructors, as well as an intervention created specifically for persons with arthritis; participants will be more willing to enroll, attend classes, and report a positive experience after completing the 8-week series.

The second aim of this study is to determine if the measures of well-being selected for this minority population are appropriate to discern facilitators and impediments for participants to view yoga as a viable option for self-care. Self-care has become increasingly important in being able to self-manage chronic disease states; however, many patients with chronic disease do not integrate self-management behaviors into their lives [88]. The concept of well-being integrates mental health (mind) and physical health (body) resulting in more holistic approaches to disease prevention and health promotion [89]. Well-being includes the presence of positive emotions and moods (e.g., contentment, happiness), and the absence of negative emotions (e.g., depression, anxiety), as well as aspects of physical, social, emotional, psychological well-being [89]. It is associated with: self-perceived health, healthy behaviors, mental and physical illness, and social connectedness [89]. For this study, self-care is defined as adopting behaviors (such as continuing to practice yoga) that improve physical and mental well-being and may decrease arthritis symptoms and side effects.

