A revised model based on Bandura’s social cognitive theory (Figure 2) shows the paths of influence believed to be relevant for this study. Bandura’s (2004) theory suggests that self-efficacy plays an important role in motivating behavior change [90]. Self-efficacy is the confidence in one’s personal ability to perform a task or behavior or to change a specific cognitive state, regardless of circumstances or contexts [91,92]. Social cognitive theory specifies a core set of determinants, among which perceived self-efficacy and knowledge of p*erceived facilitators* and *impediments* may lead to behavior changes [90,93]. Ways to influence self-efficacy include learning a new behavior, seeing people similar to oneself succeed; social persuasion; reducing negative emotional states; and correcting misinterpretations of physical ability [90,93]. The potential facilitators and impediments are measured at baseline and again at the end of the study to see if there are any changes after completing the intervention.

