*Self-efficacy* is measured using Lorig’s self-efficacy in exercise, a 3-item scale used to measure confidence in exercising regularly based on a scale from 1 (not at all confident) to 10 (totally confident) [108]. Higher scores indicate more confidence. Lorig et al. [109] and Wallen [9], have validated the 8-item Arthritis Self-Efficacy Scale (ASES) with similar populations, however the Haaz Y*oga for Arthritis* study [110] found no change when using the same ASES measure. For this pilot, the decision was made to focus specifically on using a measure related to exercise self-efficacy.

*Self-rated health* consists of a single response item, “Would you say your health in general is excellent, very good, good, fair, or poor?” [108]. Lorig et al. (1996) found the mean rating for this item to be 3.29 (*SD* ± 0.91). In a subset of their sample (*n* = 51), this item displayed a test-retest reliability of .92 [108,111]. This measure has been translated into Spanish [111]. Self-rated/self-reported health (SRH) has been differentially reported by Hispanics compared to whites, especially based on their acculturation status [111-114]. Hispanics are 3.6 times more likely to report fair or poor health compared to whites [115].

*Physical assessment* -Clinical measures were selected to evaluate domains of balance (single leg stance, functional reach test) and functional mobility (timed up and go test) that may be responsive to change with an exercise intervention. These measures are evaluated both at baseline and after completing the series of yoga classes, by the National Institutes of Health (NIH) rehabilitation medicine staff associated with the study. The *single leg stance* (SLS) determines if the patient can stand on one leg for 10 seconds [116]. When evaluated mean criterion-related validity was high (Pearson’s r =0.84, 0.83, respectively). Inter-observer reliability was high (ICC (2,1) = 0.81 at Test 1 and 0.82 at Test 2). Intra-observer reliability was high (on average ICC (2,1) = 0.88; Pearson’s r = 0.90) [117].

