This pilot study evaluates the acceptability of offering yoga as an integrative intervention for self-care using the response rate, percent of classes completed, exit interview comments and the percent of patients continuing yoga after three months. Barriers and reasons for continuing/discontinuing yoga are assessed in a brief questionnaire either in person or by telephone, three (3) months after completing yoga classes. Results from the Haaz study were used to determine reasonable measure and time frames for this study. The study found of 102 patients screened, 52% of randomized persons completed the 8-week yoga session [128]. Those who actually started the intervention were very likely to complete it, as attrition was highest prior to the first class [129]. Based on these results, the decision was made to decrease the time from enrollment to start of yoga classes; and to decrease the class size to 5–10 participants per class.

Acceptability of this study will be evaluated based on the response rate, percent of classes completed, exit interview comments and the percent of patients continuing yoga after 3 months. Feasibility will be determined based on exit interview comments and qualitative data. Qualitative field notes will be kept to monitor/document related to issues such as site capability (location/space), personnel (bilingual yoga teachers/investigators), equipment (computers/yoga props), and the amount of modifications needed. A record will be kept of eligible patients who decline and reasons for declining.

Statistical Package for the Social Sciences (SPSS) Version 20.0 will be used to analyze outcome measure data. Descriptive statistics (mean and median) will be used to describe the profiles of the subjects from demographic data gathered. Wilcoxon tests will be used to test differences between baseline and final assessments, for those who complete the study. Pre- and post- changes will be identified; however, no attempt will be made to evaluate statistical significance given the small sample size of the pilot study. An attempt will be made to complete an exit interview for all participants, even those who discontinue participation in the study prior to full completion. Missing data will be managed according to the recommendations of selected measures used in the protocol, or omitted from analyses.

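### The secondary objective asks whether the measures are appropriate, but the only analysis fixed for them is pre/post change in completers; single leg stance as worded has a ceiling at 10 seconds

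*Protocol article*

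**What the plan says.** The objectives paragraph at the end of the Background sets the question: "The secondary objective is to determine the appropriateness of specific physical and psychosocial measures for this population". The same sentence extends it to the intervention and to physical function and patient-reported measures. After Table 1, the Methods restate the second aim more narrowly, as being to "determine if the measures of well-being selected for this minority population are appropriate to discern facilitators and impediments"; the physical tests are not named there. The text on the self-care model then says how these influences will be examined: "measured at baseline and again at the end of the study to see if there are any changes after completing the intervention".

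The analysis paragraph, near the end of the Methods, fixes the comparison: "Wilcoxon tests will be used to test differences between baseline and final assessments, for those who complete the study". It adds that "no attempt will be made to evaluate statistical significance given the small sample size of the pilot study". Missing data are to follow each instrument's own rules or be left out.

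Under Physical assessment, the balance and mobility tests are chosen for domains "that may be responsive to change with an exercise intervention". Single leg stance "determines if the patient can stand on one leg for 10 seconds". By contrast, functional reach is given in inches, and the timed Up and Go and the floor transfer in seconds.

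**The concern.** A pre/post comparison answers whether scores moved. Whether a measure suits this population is a wider question: can people complete it, do they understand it in English and in Spanish, does it leave room at both ends of the scale, and does it respond to the intervention? Only the last of these is touched by change.

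The pilot's declared purpose is to inform a larger study of yoga in this population. If measures are kept or dropped on change alone, a sound measure could be dropped because 8 weeks of classes had little effect. A poor one could be kept because completers' scores drifted. Single leg stance is one of two tests named for balance, and a ceiling at 10 seconds would limit what it can say about responsiveness, the reason given for choosing it.

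**Working it through.** There is no power, alpha or effect size to reproduce; the 20 participants are a convenience sample. The check is mainly a comparison of passages, with a small illustration for single leg stance.

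**1. Objectives against the criteria named for them**

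| Objective | Criteria in the article |
|---|---|
| Primary: acceptability and feasibility | Response rate, share of classes completed, exit-interview comments, share continuing at three months; qualitative data and field notes |
| Secondary: appropriateness of the measures | None named; the measures are compared baseline to final in completers |
| Tertiary: computerized interview | Percent assistance, interviewer and participant comments, technical problems |

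Percent assistance is tied to the third objective. Participant comments are listed under self-care and well-being with no rule for judging a measure by them. The exit interview in the Appendix asks about the laptop, the classes, the room, the language of classes and future practice, but not whether the questionnaires or tests were relevant or understandable.

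**2. What change can and cannot show here**

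- Scores do not move: the measure may be unresponsive, or the intervention may have had no effect. Without a control group the two look alike.
- Scores move: this may be the intervention, practice with the test, regression to the mean or selection of completers. It does not show that items were understood or complete.
- A participant drops out or leaves items blank: this may be direct evidence of poor fit, but the person leaves the comparison or the item is handled by rule or omitted.

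**3. Single leg stance**

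Two scorings fit the wording.

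- Pass/fail at 10 seconds: those who pass at baseline cannot improve, and a gain that stays below 10 seconds (say from 3 to 8) is also invisible.
- Time capped at 10 seconds: gains below the cap are seen, but those at the cap still cannot improve.

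Under both, the number able to improve is n × (1 − p), with p the baseline share reaching 10 seconds. The documents do not give p. The assumed range is 60% to 90%; a high value is plausible because users of assistive ambulatory devices are excluded.

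- p = 0.60: 20 × 0.40 = 8
- p = 0.70: 20 × 0.30 = 6
- p = 0.80: 20 × 0.20 = 4
- p = 0.90: 20 × 0.10 = 2

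Outside that range, p = 0.50 leaves 10 and p = 0.95 leaves 1. Completion of 52%, the figure the article quotes from the earlier yoga trial, would give 0.52 × 20 = 10.4 completers. With 10 completers, 4 down to 1 could improve over the 60% to 90% range.

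**4. A yardstick for pass/fail only**

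If k participants change, all in one direction, the exact two-sided paired p-value is 2 × 0.5^k: 0.125 for k = 4, 0.0625 for k = 5 and 0.031 for k = 6. The binomial chance that at least 6 of 20 fail at baseline is 0.98, 0.87, 0.58, 0.20 and 0.01 for p = 0.50, 0.60, 0.70, 0.80 and 0.90. So the room for improvement is small at high pass rates and adequate if about half fail. The article evaluates no significance, so 0.05 serves only as a scale.

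**The case against.** The strongest reply is that the objective covers appropriateness for the intervention as well as the population, so change is legitimate evidence. That stands: change belongs in the answer, but it is not sufficient by itself.

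Second, this is a condensed article, and floor, ceiling and missing-item tables are commonly left to a fuller document. That also stands as far as detail goes. The point does not rest on absent detail. The article names criteria for its other two objectives, and what it fixes for these measures does not answer the question it sets.

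A reader might infer three stronger things that the documents do not support.

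- That pre/post change is the only analysis of any kind. Comments, field notes and percent assistance are also collected; they are just not tied to this objective.
- That the trial cannot answer its secondary objective at all. Much of the needed information is being captured, and functional reach, the timed Up and Go, the floor transfer and the questionnaires are untouched by the stance point.
- That stance is certainly pass/fail and nearly uninformative. Pass/fail is the natural reading, but no recording format is given, and the reliability figures quoted (intraclass and Pearson correlations) suit a timed score. The baseline pass rate is unknown.

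The figure of about 10 completers is likewise only a sensitivity case. The article says losses in the earlier trial came mostly before the first class, and that this study shortened the wait in response.

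**Conclusion.** The point holds in a limited form. The analysis fixed for the measures addresses responsiveness in completers, one part of the secondary objective, and cannot distinguish a poor measure from an ineffective intervention. Evidence on the other parts is either assigned to another objective or removed with missing data and non-completers. This rests on the text alone.

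The stance ceiling at 10 seconds follows from the wording under either scoring. Its size is conditional: 2 to 8 of 20 able to improve if 60% to 90% reach 10 seconds at baseline, more if fewer do. The p-values illustrate scale only. The change is worth making because it is cheap and the pilot's measures are meant to guide later work.

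**What to change.** State in the analysis section that the secondary objective will be answered by a table with one row per measure, in all enrolled participants with data, giving:

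- the percent with missing items or a missing assessment;
- the percent at floor and at ceiling;
- the percent assistance needed, for the questionnaires;
- pre/post change with a confidence interval, labelled as descriptive evidence of responsiveness only.

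Show these by language (English, Spanish) descriptively, with a note that the cells are small. Even in all 20, a share of 16 of 20 has an exact 95% interval of about 56% to 94%, so the table supports broad judgements, not fine ones.

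Record single leg stance as seconds held, state a cap above 10 seconds, and derive the 10-second result from it, so that the existing definition is kept.

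Most of the data are already collected. The costs are one extra table, a slightly longer balance test and, if assistance is now noted once per session, an entry for each questionnaire instead.
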